## Abstract

**Background:**

Suicidal behaviour and deliberate self-harm are common among adults. Research indicates that maintaining contact either via letter or postcard with at-risk adults following discharge from care services can reduce reattempt risk. Feasibility trials demonstrated that intervention through text message was also effective in preventing suicide repetition amongst suicide attempters. The aim of the current study is to investigate the effect of text message intervention versus traditional treatment on reducing the risk of suicide attempt repetition among adults after self-harm.

**Methods/design:**

The study will be a 2-year multicentric randomized controlled trial conducted by the Brest University Hospital, France. Participants will be adults discharged after self–harm, from emergency services or after a short hospitalization. Participants will be recruited over a 12-month period. The intervention is comprised of an SMS that will be sent at h48, D7, D15 and monthly. The text message enquires about the patients’ well-being and includes information regarding individual sources of help and evidence-based self help strategies. Participants will be assessed at the baseline, month 6 and 13. As primary endpoint, we will assess the number of patients who reattempt suicide in each group at 6 months. As secondary endpoints, we will assess the number of patients who reattempt suicide at 13 month, the number of suicide attempts in the intervention and control groups at 6 and 13 month, the number of death by suicide in the intervention and control groups at month 6 and 13. In both groups, suicidal ideations, will be assessed at the baseline, month 6 and 13. Medical costs and satisfaction will be assessed at month 13.

**Discussion:**

This paper describes the design and deployment of a trial SIAM; an easily reproducible intervention that aims to reduce suicide risk in adults after self-harm. It utilizes several characteristics of interventions that have shown a significant reduction in the number of suicide reattempts. We propose to assess its efficacy in reducing suicide reattempt in the suicide attempter (SA) population.

**Trial registration:**

The study was registered on Clinical Trials Registry (clinicaltrials.gov): NCT02106949, registrerd on 06 June 2014.

## Background

The construction of effective suicide-prevention and continuity of care strategies is a major challenge in the assessment and management of suicide attempters (SAs). Post-crisis management of suicidal patients varies from hospital discharge to forced hospitalization. Hospitalization rate after suicide attempt varies from 25 to 50% [1]. Fourteen to 25% of SAs treated at an emergency department (ED) reattempt suicide within the 1–2 years following discharge [2,3].

Outreach monitoring interventions via mail or phone facilitate access to care in case of recurrence in post-acute crisis patients discharged from the ED. Several studies on outreach interventions for suicidal patients have been published since 2001. The pioneer intervention was proposed by Motto et al. [4] and was based on postal contact. They proposed a follow-up in fifteen years after having started the inclusions in 1969. The objective of the postal contact was to show the patient that someone was concerned about his or her situation and maintain positive feelings towards him or her. After 5 years, a significant decrease in suicide related deaths was observed in the contacted group (versus no-contact group) of high-risk patients who refused on-going treatment. Carter et al. [5] programmed automated sent postcards. In the year following the suicide attempt, the authors reported a lower number of relapse in the contacted group, especially among women.

These positive results led to other studies exploring the effectiveness of telephone outreach (Vaiva et al. [6]). The telephone contact at one month proved, in per protocol analysis, to reduce the number of suicidal reattempts by about half over the course of one year (12% versus 21.6% in the control group). The post-hoc analysis showed no effect of the contact in first-attempters. The proposal of telephone contact was very well accepted and positively perceived by the population of this study.

In the EDGE project, a hotline was available to participants 24 hours a day, 7 days a week [7]. In the intervention group, suicide attempters repeaters rate did not differ significantly from that in the control group (15.1% vs. 17.3% at one year, 21.2% vs. 22.8% at two years). However, there was a lower number of reattempts in intervention group among suicide attempters repeaters (incidence risk ratio 0.55 at one year, and 0.49 at two years).

Vaiva and Walter proposed to construct a case management algorithm [8]. This «ALGOS» monitoring algorithm is based on the two interventions that showed a significant reduction in the number of SA repeaters: systematic telephone contact (ineffective in first-attempters) and «crisis card» (information card providing a 24/7 reachable phone number, effective only in first-attempters). Participants that were not contacted during phone call periods and participants that refused proposed healthcare can benefit from the «short letters» of Motto or the «postcards» of Carter.

A Chinese study published in 2010 proposed to use a different type of intervention that involved sending text messages to suicidal patients after discharge from the ED [9]. They sent 15 patients four text messages for four weeks following a suicide attempt. The text of the message varied for each transmission but the four text messages were the same for all patients. Although this type of intervention proved to be effective, management of large patient populations was not possible with the proposed device.

Taking into consideration the strengths and pitfalls of each of these strategies, we developed a software program that allows the transmittance of text messages to SAs. The SIAM (suicide intervention assisted by messages) software that we developed aims to simplify the inclusion of the patients and to have an optimized text sending. We assessed the technical feasibility and acceptability of this device in a pilot study [10]. Text messages provide several characteristics of existing monitoring strategies for suicide attempt repeaters. Using our software, we personalized the messages as recommended by Motto [4] and reached patients earlier than with a letter. Our software program allows us to readily personalize each message according to the required level of care. We clearly identify care services as the senders of the messages, as would have been done in a letter. Call-back numbers proposed in our messages are available 24 h per day and 7 days per week, in line with the contact strategy proposed by Evans et al. [7]. In comparison to the contact strategies by letter, access to our service was made easier as the patient simply had to press the call button on his/her telephone to contact us upon receiving the text message. Furthermore, sending a message with our device is 10 times cheaper than sending a postcard or a letter. The utilization of this monitoring system does not require the action of a clinician. All messages are written and scheduled before discharge and automatically sent over the monitoring period. Despite the variation in suicidal behaviour across the population [11], the worldwide dispersion of mobile phones could offer new perspectives in suicide reattempt prevention. As text messages utilize several characteristics of interventions that have significantly reduced the number of suicide reattempts, we propose to assess its efficacy on reducing suicide reattempt in SA population.

## Methods/design

### Aims and hypotheses

This study aims to determine whether the receipt of a text message sent regularly over a six-month period can reduce suicidal and self-harming behaviour among SAs.

We hypothesize that the routine reception of a text message during a six-month period will:Decrease the proportion of reattempters at 6 and 13 months;Decrease the number of total reattempts at 6 and 13 months;Decrease suicide deaths;Decrease suicidal ideations;Decrease intervention costs;Improve satisfaction through care services.

### Study design

The study is a 2-year multicentric randomized controlled trial conducted by the Brest University Hospital, France. Participants are adults discharged after self–harm, recruited in Brest, Lille, Rennes, Nantes, Tours, Vannes, and Saint-Nazaire. Participants will be recruited over a 12-month period. The study is a randomized controlled trial registered on Clinical Trials Registry (ClinicalTrials.gov; number: NCT02106949). It was authorized by ANSM (French Health Ministry) and approved by the Northwest IV Ethical Committee for the Protection of Patients.

### Setting

Participating centers are Brest, Rennes, Nantes, Lille, Angers, Tours, Vannes, (France) - public funded specialist mental health services for adults in the Western and Northwestern regions of France.

### Participants

Inclusion criteria are: male or female, aged 18 or older, surviving a suicide attempt, discharged from ED or Psychiatric Units (PU), hospitalized for less than 7 days, giving consent, and able to be contacted by phone.

The exclusion criteria are: refusing to participate, underage, incarcerated, under guardianship, without a mobile phone, enrolled in other trials, and in emergency situations where their state of health did not allow obtaining written consent.

In the case of discharge, a follow-up visit or planned hospitalization will be scheduled.

### Procedure

Participation in the study will be proposed to all suicidal adults referred to our psychiatric ED meeting the above criteria. In each center, adults who attempt suicide are admitted to the general ED and are evaluated by our ED psychiatrist who decides patients’ discharge or hospitalization. Patients will be enrolled after this evaluation. After enrolment, patients will be assigned to the intervention or control group, using an electronic randomization program. At month 6 and month 13, patients in both intervention and control groups will be contacted by phone for the evaluation. A trained psychiatrist will administer the evaluation.

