### Outcomes measures

As primary endpoints, we will assess the number of patients who will reattempt suicide in each group at month 6.

As secondary endpoints, we will assess the number of patients who will reattempt suicide at month 13, the number of suicide attempts in the intervention and control groups at month 6 and 13, and the number of deaths by suicide in the intervention and control groups at 6 and 13 month. In both group, suicidal ideations will be assessed at the baseline, 6 and 13-months. Medical costs and satisfaction will be assessed at month 13.

Baseline evaluation will be done in ED or PU before discharge. Socio-demographic details, including age, gender, employment, educational status, history of suicide attempt, country of birth, medical history and details of any treatment being received, will be recorded on a specifically designed, standardized questionnaire.

The Columbia Scale measures suicidal ideation and intent. It is a 25 item screening scale with items including binary variables (yes or no) and variables scales for each question. [12]. It is also available in French.

Axis-I psychiatric diagnoses will be assessed using the International Neuropsychiatric Interview (M.I.N.I.). It is a short, structured diagnostic interview developed for DSM-IV and ICD-10 psychiatric disorders [13]. With an administration time of approximately 15 minutes, it is the structured psychiatric interview of choice for psychiatric evaluation and outcome tracking in clinical psychopharmacology trials and epidemiological studies. It has been validated in French [14].

The medico-economic questionnaire (MEDEC) is a use of care services inventory including binary variables. It is carried out by the method validated by Beecham & Knapp at 13 month [15].

The satisfaction questionnaire was designed by our team [10] to assess whether such outreach system was accepted by the patients. The subjective system effectiveness will be explored to assess patients’ acceptability.

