### Randomisation/intervention

Random allocation to the intervention group and the control group will be carried out by an independent statistician and will be stratified by center study using blocked randomization and computer generated random numbers. This will be conducted using an online randomization system. This will be concealed from the research team (psychiatrist, nurse). The statistician will notify the study coordinator regarding the group allocation. Text messages will be sent by SIAM program, designed for the pilot study. Once the patient data is entered, the program will generate four independent text messages containing patient’s name, doctor's name and monitoring schedule from the date of inclusion. At any time the patient data, date of sending the text message and message content could be modified. At any time, sending messages (transmissions) could be interrupted. The number displayed on the recipient’s mobile phone was the psychiatric ED.

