### Safety and supervision

Patients are informed that they can contact the center where they have been treated at any time. Phone contact will be established by a trained psychiatrist and research assistant at month 6 and 13 to assess the outcome measures. If there is no cause for concern after the 6 month phone call evaluation, patients from each group will be informed that they will be contacted at month 13 for a new evaluation. If there are concerns about the participant, contact will be made by phone or face-to-face as to discuss the concerns. If the research fellow is concerned about the participant, an immediate referral will be made to an appropriate service. Any patient considered to be at high risk will be referred to an appropriate service.

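### Reattempts are elicited by phone from patients who know their arm, and the plan does not show how the caller stays unaware of allocation at months 6 and 13

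*Protocol article*

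**What the plan says.** Under Procedure, "patients in both intervention and control groups will be contacted by phone for the evaluation" at months 6 and 13, and "A trained psychiatrist will administer the evaluation". Safety and supervision describes the staffing differently: "Phone contact will be established by a trained psychiatrist and research assistant at month 6 and 13 to assess the outcome measures". No other source for reattempts is described.

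The only statement on concealment is under Randomisation/intervention. After describing how the allocation is generated, it says "This will be concealed from the research team (psychiatrist, nurse". Soon after comes "The statistician will notify the study coordinator regarding the group allocation". On the messages, the Background says "All messages are written and scheduled before discharge and automatically sent over the monitoring period", and Randomisation/intervention says "At any time the patient data, date of sending the text message and message content could be modified".

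Under Intervention, the texts carry the patient's name, display the psychiatric emergency hotline as sender and give a number to call. The same section describes a reminder text 48 hours before each evaluation call. The control section mentions only usual follow-up.

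Outcomes measures sets the primary endpoint at month 6. It describes a satisfaction questionnaire on whether patients accept the outreach system, and says "Medical costs and satisfaction will be assessed at month 13".

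**The concern.** Patients cannot be blinded to receiving named texts, so the person who asks about reattempts is the main place where ascertainment can be protected. Whether an overdose or a self-injury counts as a suicide attempt takes some judgement, and so does how far to probe. A caller who knows the arm may do either differently in the two groups, and the result enters the primary proportion directly.

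The article names one safeguard and does not say how it survives the follow-up calls. The month-13 questionnaire adds a way to unmask the caller, because its subject is the messaging system itself. Separately, if only the message arm is reminded before the calls, response and detection could differ by arm at month 6 as well as at month 13.

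**Working it through.** **Step 1. Who could learn the arm, and when.**

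| Route | Month 6 (primary) | Month 13 (secondary) | Basis |
|---|---|---|---|
| Patient mentions the texts | possible | possible | Patients know what they receive; nothing in the article limits disclosure |
| Satisfaction questionnaire on the system | no, not given then | possible, if asked before or among the reattempt and ideation questions | Outcomes measures; order not stated |
| Caller also handles the hotline, SIAM or the allocation | not stated | not stated | The document neither says this nor excludes it |

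The reminder text is a different mechanism. It need not unmask the caller, but it can make contact and detection unequal at both calls if controls do not get it.

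**Step 2. Reproduce the planned sample size.** Inputs from the sample size section: 18% against 9%, power 0.8. Two-sided alpha of 5% is assumed, since the section gives none.

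- Mean rate = (0.18 + 0.09)/2 = 0.135
- Uncorrected n = [1.960 × √(2 × 0.135 × 0.865) + 0.842 × √(0.18 × 0.82 + 0.09 × 0.91)]² / 0.09² = (0.9472 + 0.4032)² / 0.0081 = 225.1, so 226
- Continuity-corrected n = (225.1/4) × [1 + √(1 + 4/(225.1 × 0.09))]² = 246.8, so 247

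This matches the stated 247 per arm. The figure is not in dispute and serves only as the base for the illustration.

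**Step 3. Illustration: no true effect, events missed in the message arm.** The missed fractions are assumptions; the document gives none. Observed rates are c = 0.18 and i = 0.18 × (1 − missed fraction), with n = 247 per arm. The chance of a significant result favouring the messages is

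Φ[ (c − i − 1.960 × SE0) / SE1 ], with SE0 = √(2p̄(1 − p̄)/n), p̄ = (c + i)/2 and SE1 = √([c(1 − c) + i(1 − i)]/n).

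| Missed in message arm | Observed rates | Calculation | Chance of false benefit |
|---|---|---|---|
| 0% | 18% vs 18% | Φ(−1.960) | 2.5% |
| 10% | 18% vs 16.2% | (0.018 − 0.0664)/0.0339 = −1.43 | 7.6% |
| 20% | 18% vs 14.4% | (0.036 − 0.0650)/0.0331 = −0.88 | 19.1% |

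At the final level of 4.8% given under Statistical methods, the last two become 7.4% and 18.6%.

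**Step 4. Illustration in the other direction: true 18% against 9%, events missed among controls only.** Same formula, alpha 5%.

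| Missed in control arm | Observed rates | Power |
|---|---|---|
| 0% | 18% vs 9% | 83.5% |
| 10% | 16.2% vs 9% | 67.5% |
| 20% | 14.4% vs 9% | 46.3% |

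The 83.5% exceeds the planned 80% because this formula omits the continuity correction that gives 247.

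**The case against.** The strongest reply is that the article is silent rather than contradictory.

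- **The concealment sentence may mean allocation concealment only.** It directly follows the generation of the sequence, so this reading is fair. On that reading, though, the article states no masking of the outcome caller at all. On the other reading, masking is claimed but not secured.
- **A reader might infer that the caller belongs to the treating team.** The document does not say so. It gives the caller as a trained psychiatrist, in one place with a research assistant, while later care is with a psychiatrist of the patient's choice or a general physician. Hotline staff and callers are not said to be the same people.
- **A reader might infer that concealment cannot possibly hold.** That is too strong. The Background says the messaging needs no action by a clinician, the allocation goes to the study coordinator, and the article does not say who may edit messages. A separate caller could be kept unaware, apart from what patients disclose.
- **The month-13 questionnaire cannot reach the primary endpoint.** Correct. It matters only for month-13 results, and only if the same caller asks it before the other answers are recorded.
- **The order of questions belongs in a call script.** This has force for an article. The order is included in the fix because it is a cheap safeguard; its absence is not counted as an error.
- **The two staffing descriptions may be compatible.** An assistant could place the call and a psychiatrist conduct it. One clarifying sentence would settle this.
- **The illustration rests on assumed losses.** Agreed; both directions are therefore shown.

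What stands is that unblinded patients report the primary outcome by phone, and the described procedures do not secure a caller who is unaware of the arm.

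**Conclusion.** The point holds in a limited form. The article names the psychiatrist as concealed but does not secure this through the month-6 and month-13 calls. Disclosure by patients can affect the primary endpoint as well as the secondary ones. The questionnaire on the messaging system can affect the month-13 secondary outcomes only. The reminder, described only for the intervention, is a further possible source of unequal ascertainment at both calls.

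Neither the size nor the direction of bias can be computed from the document. Under the stated assumptions, losing 10% to 20% of message-arm events would raise the chance of a false benefit from 2.5% to about 8% to 19%. Losing the same share among controls, with the hoped-for effect real, would cut power from 83.5% to between 67.5% and 46.3%. These figures show why the matter is worth fixing; they are not estimates of what will happen.

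**What to change.** - State that whoever makes the month-6 and month-13 calls has no access to SIAM, the allocation or records of hotline contacts.
- Open each call by asking the patient not to mention any messages.
- Record and lock the reattempt answers first and the Columbia answers second. At month 13, MEDEC follows and the satisfaction questionnaire comes last.
- Record at each call whether the arm was disclosed.
- Reconcile Procedure with Safety and supervision on who assesses outcomes.
- Send the pre-call reminder to both arms or to neither, and say which.

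The cost is protocol and script wording, a slightly longer call, and keeping callers apart from SIAM. Exchanging callers between centres is not needed, and the referral pathway under Safety and supervision stays as written. Patients may still disclose their arm; the record of disclosure would show how often.

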### Intervention

Text messages are customized with each patient’s name and sent with an identical outreach schedule for each patient. We will send nine different text messages to each patient 48 hours after discharge, at day 8, day 15 and month 1, 2, 3, 4, 5, 6. All the text messages will be sent at 1 pm. The four messages will refer to: the validation of the suffering, recall of the discharge agreement, and the monitoring system, i.e. our outreach continuing care intervention.

They also will include information in regard to the monitoring doctor’s name (psychiatrist or general physician), and the date of the scheduled appointment if applicable. The contact phone number will be indicated in each text message transmission and the message will appear as sent from the psychiatric emergencies hotline number reachable 24/7. One example of the messages received by the patients will be: *“Mr X, we hope that your situation is getting better and that you could go to the Dr Y consultation (April 7th 2011 at 10 h00). You can call us for anything you may need at [name]”.* A final reminder text message will be sent 48 hours before the call-back telephone evaluation of month 6 and 13. Patients will be followed up by the psychiatrist of their choice or by their general physician. Text messaging monitoring will be proposed as an additional support to their standard of care.

